**Methods:**

A descriptive longitudinal study design will be used. The study will include women who underwent fistula repair between 2012 and 2015 at 3 fistula repair sites supported by the Fistula Care Project in Guinea (Kissidougou Prefectoral Hospital, Labé Regional Hospital and Jean Paul II Hospital of Conakry).

Participants giving an informed consent after a home visit by the Fistula Counsellors will be interviewed for enrolment at least 3 months after hospital discharge The study enrolment period is January 1, 2012 − June 30, 2015. Participants will be followed-up until June 30, 2016 for a maximum follow up period of 48 months. The sample size is estimated at 364 women.

The cumulative incidence rates of fistula recurrence and pregnancy post-repair will be calculated using Kaplan-Meier methods and the risk factor analyses will be performed using adjusted Cox regression. The outcomes of pregnancy will be analysed using proportions, the Pearson’s Chi Square (*χ*2) and a logistic regression with associations reported as risk ratios with 95 % confidence intervals. All analyses will be done using STATA version 13 (STATA Corporation, College Station, TX, USA) with a level of significance set at *P* < 0.05.

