The same authors found a proportion of pregnancies of respectively 13.16 % [18] and 4.26 % [19] in Ethiopia and 23.10 % in Malawi [20]. Delivery outcomes were poor with only 1 live birth reported in both Ethiopia and Malawi [18, 20]. Heavy work, sexual intercourse, and delivery have been reported to be associated with the recurrence of fistula [25–28]. Because sexuality and desire of children are part of women’s life after successful OF repair [18, 19, 21, 29] and recurrence of fistula and stillbirth are very common complications of delivery post OF repair [18, 20], there is a need for more well powered long term follow-up studies that could fill the existing gap of knowledge. The need to collect long-term follow-up data about fistula recurrence, subsequent pregnancies and their outcomes has already been identified among current research priorities on fistula [17]. Since, there has been no major comprehensive and well powered study initiated in a sub-Saharan African country involving women after OF repair, and for the status of the fistula at discharge is not always specified in the existing studies, we initiated this study with the following objectives:Analyse the incidence rate and risk factors of fistula recurrence up to 48 months follow up.Analyse the incidence rate and factors associated with pregnancy and pregnancy outcomes (maternal and perinatal) up to 48 months’ follow-up;

The endpoints will be recurrence of fistula, pregnancy, abortion or miscarriage, maternal, perinatal and child death at any time from hospital discharge.

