**Fig. 1 Fig1:**
[figure not shown]
Study flow chart

The primary outcome is the incidence rate of the recurrence of fistula. For the purpose of this study, recurrence of fistula includes the breakdown of a repaired fistula or the occurrence of a new fistula in study participants. At the study sites, the closure of fistula was determined at hospital discharge by a pelvic exam using a dye test. During follow-up visits, women will first be asked about current medical status using the question “does the woman have continuous and uncontrolled leakage of urine?”. If the answer is “YES” then women will be scheduled for a pelvic exam with a dye test for confirmation, at the nearest health facility (health centre or health post). This question is always used at EngenderHealth supported sites to assess women at reception, before further pelvic exam. In addition, the presence of “continuous and uncontrolled leakage of urine” is commonly used as a screening question for fistula in circumstances in which a pelvic exam is not possible (e.g. Demographic and Helath Surveys, DHS); it differentiates between fistula and other forms of incontinence, which are unlikely to be continuous and uncontrolled. In some cases, it might not be feasible to perform the dye test if for instance the woman refuses to go to a health facility. This might lead to a misclassification which can bias the estimate towards a null. However, misclassification is unlikely, since women with continued urinary leakage are eager to report their experiences in order for the condition to be rectified.

The secondary outcomes include pregnancy and pregnancy and outcomes (miscarriage or abortion or term pregnancy). Pregnancy and pregnancy outcomes will be documented by a positive pregnancy test from discharge (done at recruitment or during follow-up visit or given at any time by a result from medical records such as antenatal (ANC) card) or by a self-reporting corroborated by 2 witnesses. Maternal status at delivery and mode of delivery (dead or alive; caesarean section or normal delivery; no complication or any complication) will be assessed by looking at the ANC & Delivery card or hospital records or self-reporting. Child outcome at delivery (stillbirth, neonatal death or alive) will be assessed by looking at the ANC & Delivery card or hospital records or self-reporting corroborated by 2 witnesses.

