### Data analysis

Categorical data and treatment outcomes will be summarized as frequencies (%) and compared using *χ*2 or Fisher’s exact tests as appropriate. Continuous data will be presented using median (interquartile range) and compared using the Wilcoxon rank-sum test. Follow-up will be calculated from the date of hospital discharge. The date of fistula recurrence or the estimated date of pregnancy will be selected as the date of events. Patients who do not experience recurrence of fistula or pregnancy will be censored at the last follow up visit. For patients who are reported dead (by the relatives), the date of death will be used to determine their follow-up time in the study. For patients who are lost to follow up (i.e. who move from their village without any address to joint them after inclusion) the date of the last visit will be used.

Socio-demographic and clinical differences between those women who remain in the study and those who are lost-to-follow-up will be estimated to check for any imbalances at inclusion.

The incidence of fistula recurrence and that of pregnancy will be estimated using the method of cumulative incidence. The cumulative incidence rate will be compared across risk factors using Kaplan-Meier methods. Exposure variables with a *P*-value <0.2 in the univariate analysis will be included in multivariate models. Exposure variables with a *P*-value <0.2 in the univariate analysis will be included in multivariate models. A risk factor analysis will be performed using adjusted Cox regression. Associations will be reported as adjusted hazard ratios with 95 % CIs. Analysis will be done using STATA version 12 (STATA Corporation, College Station, TX, USA) with a level of significance will be set at *P* < 0.05.

For the outcomes of pregnancy (miscarriage or abortion, mother and child status at delivery), Pearson’s Chi square (*χ*2) will be used to compare proportions of these outcomes between potential exposure variables (age group, previous repair (Yes/No), fistula status at hospital discharge, use of antenatal care, delivery by caesarean section, etc.). Logistic regression analysis and models will be used and associations will be reported as risk ratios with a level of significance set at *P* = 0.05 and a 95 % confidence intervals.

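### Pregnancy-outcome associations are to come from logistic regression but be reported as risk ratios; the model gives odds ratios, and no conversion is stated

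*Protocol article*

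**What the plan says.** The last paragraph of the Data analysis section sets out the outcomes concerned: "For the outcomes of pregnancy (miscarriage or abortion, mother and child status at delivery". It compares proportions by Pearson's chi-square across exposures such as age group, previous repair, use of antenatal care and caesarean delivery. It then fixes the model and the effect measure: "Logistic regression analysis and models will be used and associations will be reported as risk ratios". The Methods paragraph of the Abstract repeats the pairing: "a logistic regression with associations reported as risk ratios with 95 % confidence intervals".

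The Study design section lists the categories of one of these outcomes: "Child outcome at delivery (stillbirth, neonatal death or alive". Stillbirth therefore falls under the logistic analysis.

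On frequency, the Background states: "recurrence of fistula and stillbirth are very common complications of delivery post OF repair". Of earlier series it adds: "Delivery outcomes were poor with only 1 live birth reported in both Ethiopia and Malawi".

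By contrast, for recurrence and for the occurrence of pregnancy the Data analysis section names Cox regression and the measure that belongs to it: "Associations will be reported as adjusted hazard ratios with 95 % CIs".

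**The concern.** A logistic model is linear in the log odds, so its exponentiated coefficient is an odds ratio. The article states both the model and the measure, and they do not match. The mismatch appears in two places, so it is unlikely to be a slip of the pen. It is also not a detail lost in condensing, because the article commits itself to a specific pairing.

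The label would do little harm if every outcome were rare. For stillbirth the article's own description points the other way. An odds ratio read as a risk ratio lies further from 1 in either direction, so harmful associations look stronger and protective ones more protective. Pregnancy outcomes are part of the second stated objective, the exposures include antenatal care and caesarean delivery, and the Discussion intends the results to guide policy. Readers would take a reported risk ratio as the factor by which risk changes.

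**Working it through.** **Is there a figure to reproduce?** No. No stated sample size, power or precision depends on the choice between odds ratio and risk ratio.

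**Is a conversion step stated?** The Abstract and the Data analysis section both go straight from logistic regression to risk ratios. Neither mentions a log-binomial model, Poisson regression with robust variance, or standardisation of predicted risks.

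**Which outcomes does the common-outcome argument reach?** The Background calls two things very common: recurrence of fistula and stillbirth. Recurrence goes to Cox regression with hazard ratios, so only stillbirth passes through the logistic model. Miscarriage, neonatal death and maternal death are not described this way.

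**How strong is the evidence on frequency?** The Background gives pregnancy proportions of 13.16 % among 38 women and 23.10 % among 26 women for the two series that it cites for live births:

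- 0.1316 × 38 = 5.0 pregnancies
- 0.2310 × 26 = 6.0 pregnancies

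A single live birth against about 5 or 6 pregnancies gives no support for treating stillbirth as rare. But the series are very small, and the article does not say that all the other pregnancies ended in stillbirth. They cannot supply a baseline risk.

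**Size of the discrepancy.** Let p0 be the risk in the unexposed, RR the true risk ratio, and p1 = RR × p0. Then

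OR = [p1/(1 − p1)] / [p0/(1 − p0)] = RR × (1 − p0)/(1 − p1).

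The values of p0 and RR are assumptions, because the article gives no risk by exposure group. For RR = 2.0:

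- p0 = 2 %: 2.0 × 0.98/0.96 = 2.04
- p0 = 10 %: 2.0 × 0.90/0.80 = 2.25
- p0 = 20 %: 2.0 × 0.80/0.60 = 2.67
- p0 = 30 %: 2.0 × 0.70/0.40 = 3.50

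Other true effects over the same range:

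| Assumed p0 | OR if RR = 1.5 | OR if RR = 2.0 | OR if RR = 0.5 |
|---|---|---|---|
| 2 % | 1.52 | 2.04 | 0.49 |
| 10 % | 1.59 | 2.25 | 0.47 |
| 20 % | 1.71 | 2.67 | 0.44 |
| 30 % | 1.91 | 3.50 | 0.41 |

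For RR = 2.0 the odds ratio exceeds the risk ratio by 2 % at p0 = 2 % (2.04/2.0), by 12.5 % at 10 % (2.25/2.0), by 33 % at 20 % (2.67/2.0) and by 75 % at 30 % (3.50/2.0). These are unadjusted two-by-two values; in an adjusted model the gap would also depend on the covariates.

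**The case against.** The strongest defence is that risk ratios can legitimately be obtained from a logistic model, by averaging predicted risks under each exposure level. If the investigators intend this, the reported numbers would be correct. That stands as a possibility, and it means exaggeration is not certain. It does not rescue the text, which names no such step in either place.

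A second defence is that the outcomes are secondary, the direction of each association is preserved, and the chi-square comparisons and the test of no association do not depend on the label. All of this is true and limits how serious the point is.

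Two stronger readings are tempting, and the article does not support them:

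- A reader might infer that effects on every pregnancy outcome will be exaggerated. Only stillbirth is both called very common and analysed by logistic regression. For a rare outcome, as maternal death may be expected to be, the difference is negligible (2.04 against 2.0 at a 2 % risk).
- A reader might infer that the intervals will be too narrow because a woman can contribute more than one pregnancy during follow-up. The recruitment section does say that pregnancies and their outcomes will be documented. But the Data analysis section states neither the unit of analysis nor the variance method. A condensed article may leave those to the full plan, so this silence is not an error.

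**Conclusion.** The pairing of logistic regression with risk ratios is wrong as written, in the Abstract and in the Data analysis section alike. If exponentiated coefficients are printed as risk ratios, they are mislabelled for every pregnancy outcome. The numerical consequence depends on how common the outcome is: about 2 % for a true risk ratio of 2.0 at an assumed 2 % baseline risk, rising to 33 % at 20 % and 75 % at 30 %. A material distortion can be argued from the article only for stillbirth, and its size rests on assumed risks.

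The primary outcome and its Cox analysis are untouched. So is the sample size, which rests on the precision of a confidence interval for one proportion. This should be corrected before analysis, but it does not threaten the study's main result.

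**What to change.** Make the same correction in the Abstract and in the last paragraph of the Data analysis section, in one of two ways:

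- Keep logistic regression and report odds ratios with 95 % confidence intervals. This is a change of one word in each place. Stillbirth results should then not be described in the text as ratios of risk.
- Keep risk ratios and name the method that yields them: Poisson regression with robust variance, log-binomial regression, or logistic regression followed by marginal standardisation, with the interval taken from that method.

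Either is valid. The second gives readers the measure that the article says it wants. The cost is one sentence in two places and, for the second option, a different model command or a post-estimation step. No new data are needed, and the sample size does not change.

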## Discussion

This longitudinal study will generate long-term follow-up data on fistula recurrence, subsequent pregnancies and their outcomes among women who underwent successful fistula repair in order to guide policy making and strategic planning in Guinea. This will improve current and future programmes for fistula management and care. The findings will also contribute towards improving programme performance and support advocacy efforts for better reintegration of fistula patients in Guinea and beyond.

This study has a number of strengths. First the protocol employs appropriate design and analytical methods, and a well powered sample size. Second, it will take advantage of the large collection of long term data assessing the recurrence of fistula and the outcomes of pregnancy. Third, it will add to previous studies examining fistula recurrence and reproductive outcomes after obstetric fistula repair by assessing a wide variety of variables, and by adjusting for potential confounding factors.

The results of this study and its potential implications will be made known to health care staff in the study sites, as well as the national level. National and international platforms will be used to disseminate study findings and the results will be presented at international conferences and published in peer reviewed journals. Since the findings might be applicable to other fistula care and management programmes in neighbouring countries, the lessons learnt might have wider benefit.

## Abbreviations

ANC: Antenatal care
CI: Confidence intervals
DHS: Demographic and Health Survey
GCP: Good Clinical Practice
IRB: Institutional Review Board
ITM: Institute of Tropical Medicine
OF: Obstetric fistula
RVF: Rectovaginal fistula
UNFPA: United Nations Population Fund
USA: United States of America
USAID: United States Agency for International Development
VVF: Vesicovaginal fistula
